**Table 2. Decision model for discontinuation or modification of dose escalation schedulea**

| Group               | DLT                                      |      | Action                                                                                                                                                                                                        |
|---------------------|------------------------------------------|------|---------------------------------------------------------------------------------------------------------------------------------------------------------------------------------------------------------------|
| If # of subjects is | And if # of subjects with similar DLT is |      |                                                                                                                                                                                                               |
| 3                   | 0                                        | Then | Continue with next higher dose group                                                                                                                                                                          |
| 3                   | 1                                        | Then | Expand group to 6 subjects                                                                                                                                                                                    |
| 3                   | 2 or more                                | Then | Determine if:
– this group should be expanded to 6 subjects
– previous group should be expanded to 6 subjects
– a new group should start with a lower dose b
– study should be stopped |
| 6                   | 1                                        | Then | Continue with next higher dose group                                                                                                                                                                          |
| 6                   | 2 or more                                | Then | Determine if:
– study should be stopped
– study should continue with next group and determine dose level for that group c                                                                    |

a. The nature of the DLT will be taken into account

b. Depending on the nature of the DLT, the next group can in principle receive an intermediate dose between the current dose level and the previous dose level

c. Depending on the nature of the DLT, the next group can in principle receive an intermediate dose between the current dose level and the previous dose level

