|                                                                                                                 | 
injections in total). Depending on a possible maximum tolerated dose, twelve to eighteen patients will be investigated in four groups. Each consecutive group will consist of three patients who will be treated with maximally 0.5 mg/kg, 2 mg/kg, 6 mg/kg and 10 mg/kg, respectively. Effect and safety assessments will be done at regular intervals. Prior to each dose escalation, the safety data of the first three weekly administrations of PRO051 will be reviewed. If possible dose limiting toxicity occurs in one patient of the group of three, the group will be expanded to six patients.
 
If similar dose limiting toxicity occurs in two or more patients, the inclusion of new patients will be discontinued at that dose level. Furthermore, the inclusion of new subjects into the study may be stopped, or study may continue with a lower intermediate dose level, or study may continue by expanding the cohort of the previous dose level to six subjects. The dose level of the group which has a dose level one step below the group with similar dose limiting toxicity in two or more patients, will be considered the maximum tolerated dose (MTD).
 |

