## 3 Study design

### 3.1 Overall study design

This study has been designed as an open label, multiple dose, escalating dose study. Depending on the MTD level, twelve to eighteen patients will be studied in four groups.

The study flow chart in Figure 3 outlines the dose escalation design of this study. Patients in the first group will receive 0.5 mg/kg, in the second group maximally 2 mg/kg, in the third group maximally 6 mg/kg and in the fourth group maximally 10 mg/kg.

[figure not shown]

Figure 3. Study flow chart with maximum dose levels to be administered.

Patients will receive one dose of PRO051 per week for 5 weeks. Each group will initially consist of 3 patients. Interim safety review for dose escalation will take place after review of all safety data that have been collected from at least up to and including the first three administrations of study medication (i.e. at least up to and including visit 4) for each patient and no prohibitive adverse events have been observed. In case of potentially dose limiting toxicity (DLT) in one of three patients in one group, this group will be expanded to six patients. In case of similar dose limiting toxicity in two or more patients, the inclusion of patients will be stopped at that dose level. Further, it will be decided if inclusion of new subjects should be stopped, or if the study should continue with a new lower dose group, or if the study should continue by expanding the previous group to six subjects. The dose level of the group which has a dose level one step below the group with similar dose limiting toxicity in two or more patients, will be considered the maximum tolerated dose (MTD).

The decision model for discontinuation or modification of dose escalation schedule is shown in Table 2.

Given the limited number of patients affected by DMD correctable by exon 51 skipping, an adaptive design was chosen to ensure that at least at the highest dose levels a reasonable number of patients could be included and that sufficient data on dose limiting toxicities could be collected. Furthermore, it was considered that the safety and tolerability profile warranting further investigations in a larger population could sufficiently be established with these group sizes.

No control group was included due to the limited number of patients available.

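### With two or more similar DLTs in a group of three, section 3.1 and the synopsis close the dose level, but Table 2 offers expansion of that same group to six

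*Protocol*

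**What the plan says.** Section 3.1 gives the stop rule without an exception: "In case of similar dose limiting toxicity in two or more patients, the inclusion of patients will be stopped at that dose level". It then names three ways to proceed: end inclusion of new subjects, open a group at a lower dose, "or if the study should continue by expanding the previous group to six subjects". The maximum tolerated dose (MTD) is the level "one step below the group with similar dose limiting toxicity in two or more patients".

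The synopsis (design and methodology) repeats the rule: "If similar dose limiting toxicity occurs in two or more patients, the inclusion of new patients will be discontinued at that dose level". It gives the same three routes, and the only expansion among them is that the "study may continue by expanding the cohort of the previous dose level to six subjects".

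Table 2, which section 3.1 presents as the decision model, has a row for three subjects with two or more similar DLTs. It lists four options. One is "this group should be expanded to 6 subjects"; the next line is "previous group should be expanded to 6 subjects". The other two are a new group at a lower dose and stopping the study.

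**The concern.** The trigger is the same in all three places: similar DLT in at least two patients. The text forbids further inclusion at that dose, while the table permits three more inclusions there. A site or sponsor acting on Table 2 would break section 3.1, and one acting on section 3.1 would be ignoring an option in the decision model.

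This is a safety rule for boys aged 5 to 16 in a dose escalation study. Section 3.1 says that the five-injection phase is meant to establish the MTD and a dose for later studies. The rule that governs when a dose is closed should have one reading, and the looser reading allows exposure at a level already found to be toxic.

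**Working it through.** **1. The two option lists for three subjects with two or more similar DLTs**

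| Action | Section 3.1 | Synopsis | Table 2 |
|---|---|---|---|
| Inclusion closed at this dose | yes, no exception | yes, no exception | not stated |
| Stop | yes | yes | yes |
| Lower dose | yes | yes | yes |
| Expand the previous group | yes | yes | yes |
| Expand the current group | no | no | **yes** |

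The current and previous groups stand on separate lines of Table 2, so the first cannot be a slip for the second within that row.

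**2. Do the footnotes reconcile them?** Footnote a says that the type of DLT will be considered. It applies to the whole table and does not mention the stop rule. Footnotes b and c concern an intermediate dose for the next group. None allows more patients in the current one. The word *similar* does not separate the cases either, because both the stop rule and the column heading of Table 2 require it.

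**3. What could expansion achieve?** Let x be the similar DLTs in the first three subjects and y those in the three added, with y = 0, 1, 2 or 3.

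- x = 2: total 2 + y = 2 to 5 of 6.
- x = 3: total 3 + y = 3 to 6 of 6.

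The minimum is 2 of 6. The six-subject row that leads to the next higher dose needs exactly 1, so it cannot be reached. Every outcome falls in the row for two or more of six, where the choice is to stop or that the "study should continue with next group and determine dose level for that group". Footnote c to that row names only a dose between the current and the previous level. The MTD stays one step below, whatever the result.

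**4. Maximum extra exposure.** Inputs are the group sizes of 3 and 6 (section 3.1 and Table 2), dosing on days 1, 8, 15, 22 and 29 (section 3.2.1), and the dose levels (section 3.1).

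- Extra boys: 6 − 3 = 3, and 3/18 = 17% of the largest planned sample.
- Extra injections: 3 × 5 = 15.
- Cumulative dose per boy: 5 × 10 = 50 mg/kg at the top level; 5 × 6 = 30 mg/kg at the third.

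**5. How often would the row be met?** The protocol gives no DLT rate, so the rates p below are assumptions. They treat patients as independent and all DLTs as similar. The chance of reaching the row is 3p²(1 − p) + p³. The chance of at least one further DLT among three added boys is 1 − (1 − p)³.

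| Assumed p | Row reached | Further DLT if expanded |
|---|---|---|
| 10% | 0.028 | 0.271 |
| 20% | 0.104 | 0.488 |
| 30% | 0.216 | 0.657 |
| 40% | 0.352 | 0.784 |
| 50% | 0.500 | 0.875 |

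These figures only illustrate scale. The contradiction does not depend on them.

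**The case against.** The best defence has four parts.

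- **Purpose.** Section 3.1 says the adaptive design should secure a reasonable number of patients at the highest doses and enough data on DLTs. Expanding a toxic group would add such data and could inform the dose of the next group. This is a possible motive, but the same section stops inclusion at that dose, so the motive does not authorise the option.
- **Discretion.** The row asks for a decision and does not order expansion. A data monitoring committee oversaw the core part (section 8.3), and the next dose could be lowered (section 3.2.1). This makes misuse less likely. It does not make the two lists agree.
- **Ceiling.** The 15 injections assume that the option is chosen, all three places are filled and every boy completes dosing. Withdrawal after a related serious adverse event (section 4.5) and staggered starts (section 3.2.4) would tend to reduce this. That is right, and the figure should be read as an upper limit.
- **Spent rule.** Section 8.3 describes the core dose escalation as finished. No analysis or current patient depends on the line. This stands and removes any urgency.

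**Conclusion.** The contradiction holds. Table 2 allows an action that section 3.1 and the synopsis rule out under the same trigger, and nothing in the protocol reconciles them. The option cannot clear the dose or change the MTD. Its only effects are up to three more boys treated at a closed level and whatever further toxicity data they yield. This assumes that events once counted as similar DLTs stay counted.

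The protocol does not say whether any group reached this row. With escalation complete, the point concerns the rule on record and any later protocol that borrows it. It should be corrected, but it is not urgent.

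**What to change.** Delete the option to expand the current group from the Table 2 row for three subjects with two or more similar DLTs. The three remaining options then correspond to those in section 3.1 and the synopsis. If the sponsor did intend an exception, it would instead have to be written into both of those places with the circumstances that justify it. Deletion is simpler and safer. Figure 3 is not visible in the copy reviewed and should be checked for the same option.

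The cost is one line of one table, with no new rule, data or procedure. Because the line belongs to a safety rule, the change may count as substantial under section 9.6 and need ethics committee and competent authority approval. Putting it into the next amendment avoids a separate submission.

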## 3.2 Study treatments

### 3.2.1 Treatments administered

Successive cohorts of 3-6 patients will receive PRO051 by subcutaneous injection on day 1, 8, 15, 22 and 29. The number of injection sites per administration depends on the total dose to be administered but will not exceed two injection sites.

Patients in the first group will receive 0.5 mg/kg, in the second group maximally 2 mg/kg, in the third group maximally 6 mg/kg and in the fourth group maximally 10 mg/kg.

Dose escalation will only take place after review by the investigators and the medical responsible person of the sponsor as described in section 3.1.

If review of the safety data raises concerns about the next dose level to be administered, the dose level may be adjusted downwards. If this occurs, the IEC/IRB and regulatory authorities if applicable will be notified of changes in planned dose levels.

### 3.2.2 Selection of doses administered

The dose levels for the escalating dose levels were selected on the basis of available animal toxicological data and past clinical experience with chemically related phosphorothioate oligonucleotides (see also section 1.3 and 1.4).

### 3.2.3 Selection and timing of dosing for each patient

Study medication will be administered five times to each patient with an interval of one week between administrations. Injection will preferably be given in the morning and always at approximately the same time of the day.

### **3.2.4      Method of assigning subjects to treatment groups**

This is an open study in which all study subjects will receive active treatment. Patients will be assigned to a dose level based on the sequence of entering the study.

For safety reasons, there will be an interval of at least 2 days between the start of treatment of each patient within one group.

### **3.2.5      Blinding**

Not applicable.

### **3.2.6      Treatment compliance**

Administration of study medication and any deviation thereof will be recorded on the appropriate CRF.

## **3.3      Study evaluations**

Appendix 2 depicts the schedules of assessments throughout the study. Table 4 shows the assessments to be done during the study period (visit 1 – 12). Table 5 specifies the assessments to be done during each hospitalization visit (visit 2 – 6). In Tables 6 - 14 is depicted the schedule of assessments to be done during the treatment beyond study.

Total blood volume during the study period to assess effect, safety laboratory and pharmacokinetic parameters is maximally 200 ml for each study participant, divided over 13 visits during a 18-week (4 ½ months) period. Main burden will be during the 5-week treatment period.

In the treatment beyond study period, the total blood volume to assess effect, safety laboratory and pharmacokinetic parameters is for each study participant as follows.

- maximally 140 ml during the period of the 1st week visit u/l the 13th week visit. Main burden will be at week 1, 5, 9, and 13.
- maximally 125 ml during the period of the 14th week visit u/l the 25th week visit. Main burden will be at week 17, 21, and 25.
- maximally 135 ml during the period of the 26th week visit u/l the 49th week visit. Main burden will be at week 29, 33, 37, 41, 45, and 49.
- maximally 122 ml during the period of the 50th week visit u/l the 73rd week visit. Main burden will be at week 53, 57, 61, 65, 69, and 73.
- maximally 157 ml during the period of the 74th week visit u/l the 97th week visit. Main burden will be at week 77, 81, 85, 89, 93, and 97.
- maximally 157 ml during the period of the 98th week visit u/l the 121nd week visit. Main burden will be at week 101, 106, 109, 113, 118 and 121.
- maximally 157 ml during the period of the 122nd week visit u/l the 145th week visit. Main burden will be at week 125, 130, 133, 137, 142, and 145.
- maximally 157 ml during the period of the 146th week visit u/l the 169th week visit. Main burden will be at week 148, 154, 157, 161, 166 and 169.
- maximally 157 ml during the period of the 170th week visit u/l the 193rd week visit. Main burden will be at week 172, 177, 180, 184, 189 and 192.
- maximally 157 ml during the period of the 194th week visit u/l the 217th week visit. Main burden will be at week 196, 201, 204, 208, 213 and 216.

All remaining test material (clinical trial samples) will be stored under the required storage conditions for at least 3 months after completion of the Analytical Report, with a maximum of one year. Destruction will be authorized, documented and archived. However, additional

written consent has been obtained for unlimited storage and future use of biological samples for medical scientific research.

### **3.3.1      Treatment period**

Treatment visits take place on day 1, 8, 15, 22 and 29. Subjects will be admitted to the hospital for an overnight stay on the treatment days. Baseline assessments will be done at time point 3 to 0 hours prior to dosing. Then PRO051 is administered by a maximum of 2 subcutaneous injections (depending on the total dose to be administered) in the abdomen located at least 4 cm apart ( $t=0$  day 1, 8, 15, 22 and 29). Subjects will be monitored for approximately 30 hours (one night), during which all safety and laboratory assessments, adverse events and other assessments as indicated in the Schedule of assessments will be completed (Appendix 2: Table 5). Thereafter, the subjects can return home. On the third day after discharge (i.e.  $t=96\pm6$  hrs after dosing) patients will be contacted by telephone by the investigator to enquire about adverse events and concomitant medication.

### **3.3.2      Follow-up period during study**

Follow-up visits take place on Days 36, 43, 57, 78, 99 and 120.

Assessments as indicated in the Schedule of assessments (Appendix 2: Table 4) will be made during each of these follow-up assessments.

All subjects will have an 8 week interruption to drug administration, following completion of Visit 85 (or as soon as Amendment 7 is approved after Visit 85). During the 8 weeks off drug, subjects will be asked to return for Visit 89 where safety parameters and efficacy measures will be made. Additional visits can be arranged depending on the current clinical status of the

subject and the clinical judgement of the investigator. Subjects will then re-start study administration according to a dosing regimen of;

- Subjects will receive one dose of 6 mg/kg PRO051 per week x 8 weeks if their body weight is  $\leq 50$  kg. This will be followed by 4 weeks off drug. This will continue in a cyclical manner.
- If a subjects body weight  $>50$  kg, he will receive one maximal dose of 300 mg PRO051 per week x 8 weeks This will be followed by 4 weeks off drug. This will continue in a cyclical manner.

Based on PK/PD modelling this regimen is predicted to result in an overall 12-week exposure that is somewhat lower than the continuous dosing regimen. The dystrophin levels are predicted to fluctuate between about 70% of the current level at the end of the off drug period, to about 80% at the end of the 8 weeks on drug. Although a compromise in efficacy is not anticipated, the impact on response will be closely monitored and if a perceived continuous decline in efficacy is observed, the investigator will discuss the potential benefit for an individual subject to return to continuous weekly dosing at 6mg/kg PRO051 with the Medical Monitor where the safety and tolerability is acceptable. The intermittent dosing regimen may, however, help to minimize organ burden from accumulation of this compound in organs, such as liver and kidney by allowing organs to washout during the off-treatment period. The overall risk benefit profile will be regularly assessed. Any change from intermittent dosing to continuous weekly dosing will be implemented at the start of a 12 week cycle.

The treatment with PRO051 beyond the study period should comply with the following conditions:

- Subject benefits from the PRO051 treatment
- Safety and effect assessments are performed as described in Appendix 2: Table 6, Table 7, Table 8 and Table 9.
- Maximum treatment period is until (whichever comes first):
  - the start of a next trial with PRO051 for which the subject is eligible, or
  - is exposed to safety risks outweighing potential benefits, or
  - PRO051 no longer appears to improve or stabilize the clinical status of the patient, or
  - development program of PRO051 is halted or discontinued, or
  - marketing authorization of PRO051 has been obtained, or
  - sponsor is not able to supply PRO051 anymore, or
  - sponsor decides to stop further clinical development of PRO051 (taking into account a reasonable term of notice), or
  - sponsor decides to stop further production of PRO051 (taking into account a reasonable term of notice).
- If there are possibilities for reimbursement of PRO051 during the treatment beyond study period but prior to marketing authorization, sponsor may ask the support of investigator to help in arranging for such reimbursement, if feasible.

### **3.3.4 Efficacy evaluations**

The following parameters will be used to evaluate efficacy: dystrophin expression in muscle biopsy, PRO051 levels in muscle biopsy, mRNA production in peripheral blood mononuclear cells, timed tests (10-meter walk/run test, timed rising from floor, stair climb), 6-minute walk test, Quantitative Muscle Testing (QMT) and Manual Muscle Testing (MMT).

These evaluations will be performed at visits as shown in Appendix 2.

### **3.3.5 Safety evaluations**

The following parameters will be used to evaluate safety: the assessment of AEs that may have occurred between each of the visits, physical examination, vital signs, ECG, routine biochemistry (sodium, potassium, calcium, urea, creatinine, ASAT, ALAT,  $\gamma$ -GT, LDH, ALP, CK, bilirubin, amylases, total protein, albumin, glucose, cholesterol), routine hematology (hemoglobin, MCV, erythrocyte count, hematocrit, MCH, MCHC, reticulocyte count, thrombocyte count, leukocyte count, leukocyte differential count: basophils, eosinophils, lymphocytes, monocytes, neutrophils), coagulation (aPTT), urinalysis (dipstick and quantitative protein and creatinine), complement activation (C3a, SC5b-9 and Bb), inflammatory response (IL-6, TNF- $\alpha$  and MCP-1) and immune response (dystrophin antibodies in blood), local tolerability at the injection site(s).

These evaluations will be performed at visits as shown in Appendix 2.

